**Definition of Outcome Measures:**

*Sputum culture conversion at 2 months*: The proportion of patients with negative sputum cultures at 2 months of treatment.

*Favourable bacteriological response at end of treatment:*

A patient will be classified as having had a 'Favourable' bacteriological response at end of treatment if all three cultures are negative in the last month of treatment.

*Unfavourable bacteriological response:*

A patient will be classified as having had an 'Unfavourable' bacteriological response at end of treatment if more than one culture is positive in the last month of treatment, one of which is at least 20 colonies or more.

*Doubtful bacteriological response:*

A patient will be classified as having had a 'Doubtful' bacteriological response if one or more cultures are positive in the last month of treatment, none of which is 20 colonies or more.

The physicians acting in consultation can decide on a change of treatment based on clinical and/or radiological deterioration and persistent sputum positivity. Such cases will be put up to the Panel for ratification of the decision.

*Relapse after treatment:*

In patients who have had a favourable or doubtful bacteriological response at the end of treatment, relapse during follow-up is defined as either I) two positive sputum cultures in a 2-month period, one of which is at least 20 colonies, (such patients will be retreated if at least one sputum smear is also positive)

or ii) positive sputum cultures during four consecutive monthly examinations, one of which is at least 20 colonies.

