**Sample size:**

Applying an equivalence design and

assuming that the efficacy of the control regimen (Regimen 3) will be 95% (0.95) in patients with drug susceptible disease, taking into account both failures at the end of treatment and relapse over 24 months,

Type I error to be 5% (0.05, 1 tail) Z = 1.64 and

Type II error to be 10% (0.1) Z = 1.28 and

the definition of equivalence as 5% (0.05),

the sample size required for each regimen was calculated to be 2 (0.95 x 0.05) (1.64 + 1.28)2/(0.05)2 = 323.

Sample size for 3 regimens = 3 x 323 = 969

Loss in follow-up over 24 months is expected to be 10% (0.01)

Proportion of patients with drug resistant tuberculosis at intake is expected to be 10% (0.01)

The required sample size for the trial will therefore be 969/ (0.9 x 0.9) = 1196 or approximately 1200 patients

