Blood sugar, blood urea, serum creatinine, serum uric acid, serum bilirubin, serum alanine and aspartate transaminase, serum alkaline phosphatase and gamma glutamy transaminase (GGT) at the time of the 2nd and 4th monthly examinations.

*During follow-up:*

After treatment is completed all patients will be followed up every month for 24 months (28 to 30 months from start of treatment). During these monthly visits the following evaluations/ investigations will be done:

Clinical examination

Weight will be recorded

Two sputum specimens will be examined by smear (fluorescent microscopy) and culture (LJ medium) for *Mycobacterium tuberculosis* and identification and drug susceptibility tests for isoniazid, rifampicin, ethambutol, moxifloxacin and gatifloxacin will be carried out on positive cultures.

Urinalysis will be done for albumin, acetyl isoniazid, rifampicin and cytology.

In addition,

X-ray Chest PA view will be done at the 12th monthly examination and at the end of treatment.

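### The four-month relapse criterion adds no case to the two-month one, so patients persistently culture-positive below 20 colonies are never counted as relapses

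*Supplement*

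**What the plan says.** Under Definition of Outcome Measures, the population at risk and the form of the rule are set by "In patients who have had a favourable or doubtful bacteriological response at the end of treatment, relapse during follow-up is defined as either" one of two criteria:

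- Criterion (i): "two positive sputum cultures in a 2-month period, one of which is at least 20 colonies". A retreatment clause is attached to this criterion only: "such patients will be retreated if at least one sputum smear is also positive".
- Criterion (ii): "or ii) positive sputum cultures during four consecutive monthly examinations, one of which is at least 20 colonies".

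The same section classes a patient as Doubtful at the end of treatment "if one or more cultures are positive in the last month of treatment, none of which is 20 colonies or more". The 2005 amendment adds the patient with a single positive culture to the Doubtful class. None of the amendments shown changes the relapse definition.

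Under Clinical assessments and Investigations, "After treatment is completed all patients will be followed up every month for 24 months", and at each of these visits "Two sputum specimens will be examined by smear (fluorescent microscopy) and culture (LJ medium").

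Under Sample size, control efficacy is taken as 95%, "taking into account both failures at the end of treatment and relapse over 24 months", and equivalence is defined as 5 points.

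**The concern.** Two criteria joined by an either/or should each be able to identify a patient whom the other misses. A rule based on four months of persistence would naturally add patients whose cultures stay positive without a high count. Because criterion (ii) repeats the 20-colony condition, it cannot do this.

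The Doubtful class extends the gap back to the end of treatment. A patient with all three last-month cultures positive below 20 colonies is Doubtful, and the relapse definition then treats Doubtful patients as still at risk of relapse, which implies that they are not failures. Such a patient could be culture-positive at every follow-up visit below 20 colonies and have no unfavourable outcome recorded under these definitions.

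Relapse is part of the efficacy measure used to size the trial. In an equivalence comparison, unfavourable outcomes that go uncounted narrow the observed difference if they fall mainly in the shorter regimens.

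**Working it through.** **Inputs.** From Definition of Outcome Measures: criteria (i) and (ii) and the Doubtful class. From Clinical assessments and Investigations: monthly follow-up visits with two cultures each. From Sample size: efficacy 0.95, margin 0.05, z = 1.64 and 1.28, 323 per regimen.

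**The plan's own figure.** 2 × 0.95 × 0.05 × (1.64 + 1.28)² / 0.05² = 0.095 × 8.5264 / 0.0025 = 324.0, against 323 printed. 969 / (0.9 × 0.9) = 1196.3, against 1196 printed. Both agree to within rounding, and the point does not depend on them.

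**Step 1: criterion (ii) is contained in (i).** Take any run of four consecutive positive months in which some month has a culture of at least 20 colonies. That month has at least one neighbour inside the run, and the neighbour is positive. The two months together give two positive cultures in a 2-month period, one of at least 20 colonies, which is criterion (i).

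This was checked by listing every possible pattern with two cultures per month, each negative, positive below 20, or positive at 20 or more. The 2-month period was read as two or as three monthly examinations, and the two positives were either allowed at the same visit or required at different visits.

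| Consecutive months | Patterns meeting (ii) | Meeting (ii) but not (i), all four readings |
|---|---|---|
| 4 | 4,015 | 0 |
| 5 | 40,555 | 0 |
| 6 | 402,750 | 0 |

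The four-month figure can be checked by hand. A positive month has 3² − 1 = 8 possible states, of which 3 have no count of 20 or more, so 8⁴ − 3⁴ = 4,096 − 81 = 4,015.

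**Step 2: low-count persistence meets neither criterion.** Patterns positive in every month with all counts below 20 number 81, 243 and 729 over 4, 5 and 6 months. None is a relapse as written. All would be if four consecutive positive months counted at any colony count. This step does not depend on how the 2-month period is read.

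**Step 3: a longer horizon.** With one result per month over ten months there are 3¹⁰ = 59,049 patterns, and 33,200 contain four or more consecutive positive months. Of these, 520 meet neither criterion if the 2-month period spans two examinations, and 320 if it spans three. In 251 of them, under either reading, every positive count is below 20. These are counts of possible patterns, not patient frequencies.

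**Step 4: what one missed case is worth.** Expected unfavourable outcomes per arm are 0.05 × 323 ≈ 16. One net missed case moves the difference by 1/323 = 0.31 points. For an assumed net excess of missed cases in one arm:

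| Net missed cases (assumed) | Shift, points | Share of the 5-point margin |
|---|---|---|
| 0 | 0 | 0% |
| 1 | 0.31 | 6% |
| 3 | 0.93 | 19% |
| 6 | 1.86 | 37% |

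If instead the same fraction f of unfavourable outcomes is missed in every arm, a true 5-point difference shrinks by 5f points: 0.25 to 0.5 points for f of 5 to 10%, and 1 to 2 points for f of 20 to 40%.

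**The case against.** The strongest reply is that redundancy by itself misclassifies nobody. The 20-colony cut-off also separates Unfavourable from Doubtful, so it looks like one deliberate threshold applied throughout. A reader might infer that its presence in criterion (ii) is a slip and that low-count patients were meant to be caught. The text does not show that intention. This part of the reply stands.

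Criterion (ii) may also have had a retreatment purpose. The smear condition is attached to (i) only, so (ii) could be meant for smear-negative patients whose cultures stay positive. That is possible, but it would not give (ii) any role in counting relapses.

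Containment needs a rolling 2-month period. With fixed two-month blocks (months 1–2, 3–4 and so on) it can fail. For example, month 1 is negative, month 2 has one positive culture of at least 20 colonies, and months 3 to 5 are positive below 20. That pattern meets (ii) but not (i). Widely spaced consecutive examinations after missed visits could have the same effect. The text suggests neither reading, and the low-count gap remains under both.

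Such patients are not invisible. Doubtful response is itself compared between regimens, physicians may change treatment for persistent sputum positivity with Panel ratification, and discharge requires negative final-month cultures. None of these provisions assigns a relapse or failure outcome. No analysis plan is shown, and one might settle how Doubtful patients enter the efficacy analysis.

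Finally, replacing the relapse definition outright would reach into retreatment, because the definition contains a retreatment clause and Ethical Considerations ties treatment to relapse. It would also follow the review of interim findings recorded in the 2006 amendment. Both objections stand and limit the remedy.

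**Conclusion.** The definitional point holds. On a rolling 2-month period, criterion (ii) adds no relapse. On any reading, a patient positive at four or more consecutive monthly examinations with every count below 20 is not a relapse. If Doubtful at the end of treatment, that patient is not a failure either; this last step rests on the relapse definition keeping Doubtful patients at risk of relapse.

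The size is unknown. The documents give no frequency of persistent low-count positivity. What can be said is that each net missed case is worth about 0.3 points at 323 per arm.

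Two stronger readings are tempting and are not supported. One is that the rule biases the trial towards equivalence by a material share of the margin. That requires such patients to be more frequent in the 4-month arms, and the documents say nothing on this; the effect could be zero. The other is to treat the 520 patterns as a measure of how often relapse is missed. They are unweighted possibilities, 520 / 33,200 = 1.6% of those with a four-month positive run, and they carry no information on patients.

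**What to change.** 1. Reconcile the two criteria so that (ii) has a stated function distinct from (i), and say whether the 2-month period is rolling. Decisions on retreatment stay with the investigators, and this point proposes no change to them.
2. For outcome classification only, prespecify, before any further between-arm comparison, an analysis in all three regimens that counts positive cultures at four consecutive monthly examinations, at any colony count, as unfavourable.
3. Report that analysis beside the result under the definition as written. Interim findings had already been reviewed, so the added analysis should not silently replace the existing one.

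The cost is a short amendment and a re-run of the classification. The existing definitions already require colony counts, so no new specimens are needed. The downside is that a few more unfavourable outcomes may be counted in each arm.

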**Clinical assessments and Investigations:**

*Baseline:*

History of present complaints and past medical history.

Detailed clinical examination including testing for aquity of vision and colour vision.

Detailed history of previous treatment for tuberculosis and history of use of quinolones and anti-arrhythmic medication. All available prescriptions slips will be scrutinized and recorded.

Assessment by a social worker for domestic stability, family history, occupational history and sociological suitability for likely adherence to treatment protocol.

Home visit by a social worker and health visitor.

At least four sputum specimens will be examined by smear (fluorescent microscopy) and culture (with LJ medium) for *Mycobacterium tuberculosis*. Positive cultures will be identified by catalase production at 68°C and PNB test. Drug susceptibility tests for streptomycin, isoniazid, rifampicin, ethambutol, moxifloxacin and gatifloxacin will be done on positive cultures.

X-ray chest PA view

Urinalysis for albumin, sugar, bile pigments, acetyl isoniazid, rifampicin and for cytology.

ECG in 12 leads. The ECGs will be interpreted by a cardiologist.

Total and differential white cell counts, red blood cell count, haemoglobin estimation, platelet count.

Random blood sugar, blood urea, serum creatinine, serum uric acid, serum bilirubin, serum alanine and aspartate transaminase, serum alkaline phosphatase and gamma glutamy transaminase (GGT).

ELISA for HIV antibodies.

*During treatment:*

Every month during the treatment phase the following will be done:

Clinical examination

Weight will be recorded

Monitoring for adverse reactions to drugs, especially moxifloxacin and gatifloxacin.

Three sputum specimens will be examined by smear (fluorescent microscopy) and culture (LJ medium) for *Mycobacterium tuberculosis* and identification and drug susceptibility tests for isoniazid, rifampicin, ethambutol, moxifloxacin and gatifloxacin will be carried out on positive cultures.

ECG in 12 leads

Urinalysis will be done for albumin and cytology

X-ray Chest PA view at the 2nd monthly examination and at the end of treatment

Total and differential white cell counts, red blood cell count, haemoglobin estimation and platelet count at the time of the 2nd and 4th monthly examinations.

Blood sugar, blood urea, serum creatinine, serum uric acid, serum bilirubin, serum alanine and aspartate transaminase, serum alkaline phosphatase and gamma glutamy transaminase (GGT) at the time of the 2nd and 4th monthly examinations.

*During follow-up:*

After treatment is completed all patients will be followed up every month for 24 months (28 to 30 months from start of treatment). During these monthly visits the following evaluations/ investigations will be done:

Clinical examination

Weight will be recorded

Two sputum specimens will be examined by smear (fluorescent microscopy) and culture (LJ medium) for *Mycobacterium tuberculosis* and identification and drug susceptibility tests for isoniazid, rifampicin, ethambutol, moxifloxacin and gatifloxacin will be carried out on positive cultures.

Urinalysis will be done for albumin, acetyl isoniazid, rifampicin and cytology.

In addition,

X-ray Chest PA view will be done at the 12th monthly examination and at the end of treatment.

**Follow-up:**

Patients will be followed up for 24 months after treatment completion (28 to 30 months from start of treatment). They will be discharged from the study after the final month culture results are negative.

**Funding:**

The study will be funded solely by the Tuberculosis Research Centre

**Ethical Considerations:**

Patients will be informed in their mother tongue or a language that they understand, about the purpose of the study and the investigations that will be carried out to make a diagnosis and to monitor the response to treatment, and the frequency with which they will have to attend the treatment centre for supervised treatment. They will be informed of the drugs that will be used to treat them and the side effects that may occur due to the drugs. A Patient Information Sheet will be made available to the patient. Their consent will be obtained with reference to the investigations that will be carried out, the frequency of their attendance at the treatment centre, and their willingness to permit visits to their homes. Counseling will be done and a separate consent obtained before drawing blood for HIV antibody testing.

Any patient who does not respond to the treatment regimen and those who relapse during the period of follow-up will be treated with an appropriate regimen.

All diagnostic procedures and treatment will be entirely free for the patients.

Patients will be informed of their right to withdraw from the study at any time, without any penalty, if they so desired.

*Age of participants*:

There have been reports of the effect of fluoroquinolones on cartilage in animal experiments. Keeping this in view we had recruited only adult patients for the TRC ofloxacin studies. In this study also we will confine the study subjects to adults of 18 years and above, till there is categorical proof that moxifloxacin and gatifloxacin are safe for children, and do not affect bone growth.

In place of “Patients allocated to regimens 1 and 2 will receive 27 doses each in the intensive and continuation phase respectively” amended as “Patients allocated to regimens 1 and 2 will receive 26 doses each in the intensive and continuation phase respectively”.

Page 5: Treatment Regimens:

Lines 18 and 19:

In place of “Patients allocated to regimen 3 will receive 27 doses in the intensive phase and 54 doses in the continuation phase: amended as “Patients allocated to regimen 3 will receive 26 doses in the intensive phase and 52 doses in the continuation phase”.

Page 7: Definition of Outcome Measures:

Doubtful bacteriological response:

Line 13:

After the sentence “A patient will be classified as having had a 'Doubtful' bacteriological response if one or more cultures are positive in the last month of treatment, none of which is 20 colonies or more” add “or has one culture positive in the last month of treatment”.

Page 8: Clinical assessments and Investigations:

*Baseline:*

Line 11-13:

In place of “Drug susceptibility tests for streptomycin, isoniazid, rifampicin, ethambutol, moxifloxacin and gatifloxacin will be done on positive cultures” amended to read as “Drug susceptibility tests for isoniazid, rifampicin, ethambutol and ofloxacin will be done on positive cultures. If the culture is resistant to isoniazid, rifampicin and ofloxacin, then drug susceptibility tests will be done for streptomycin, gatifloxacin and moxifloxacin”.

Page 9: Clinical assessments and Investigations:

*During treatment:*

*Line 1 and 2:*

In place of “susceptibility tests for isoniazid, rifampicin, ethambutol, moxifloxacin and gatifloxacin will be carried out on positive cultures”, amended to read as “drug susceptibility tests for isoniazid, rifampicin, ethambutol and ofloxacin will be carried out on positive cultures. If the culture is resistant to isoniazid, rifampicin and ofloxacin, then drug susceptibility tests will be done for streptomycin, gatifloxacin and moxifloxacin”.

Page 9: Clinical assessments and Investigations:

*During follow-up*

*Lines 7-9:*

In place of “drug susceptibility tests for isoniazid, rifampicin, ethambutol, moxifloxacin and gatifloxacin will be carried out on positive cultures”, amended to read as “drug susceptibility tests for isoniazid, rifampicin, ethambutol and ofloxacin will be carried out on positive cultures. If the culture is resistant to isoniazid, rifampicin and ofloxacin, then drug susceptibility tests will be done for streptomycin, gatifloxacin and moxifloxacin”.

Page 9: Clinical assessments and Investigations: During treatment:

Line 12:

Add “In addition, blood urea and serum creatinine will be done at 1st and 3rd monthly examinations also”. This has been recommended by the Data Safety Monitoring Board.

**27th December 2003**

Following review of the interim findings of the above study, and recommendations by the DSMB on 14th October 2006, and by the Ethics Committee Meeting of 4th November 2006, and the decision taken by the Clinic Doctors Meeting of 13th November 2006, the above protocol is being amended as follows:

Page 5, Regimen 1:

For the patients admitted to 2MHRZ3/2MHR3 regimen, moxifloxacin will be terminated from 15.11.06 and the treatment will be modified as follows:

In the Intensive Phase, patients will receive EHRZ3 instead of MHRZ3.

In the continuation phase patients will receive HR3 instead of MHR3.

At the end of 4 months HR3 will be extended for 2 more months.
